### 2.7. Outcome Measurements and Data Collection Methods

The assessment of the study outcome-related variables will take place at the baseline and at 6 months post–group assignment (Table 3).

### 2.8. Sample Size

The sample size was determined by the objective of estimating the primary outcome of the study. The standard deviation and expected difference in disease-related QoL between groups for the sample size were based on data from studies of IBD patients assessed with SIBDQ. The standard deviation was taken to be 12.52 points based on the study by Sun et al. [27]. The expected difference between the study groups was chosen to be smaller than the clinically significant change in HRQoL according to Jowett et al. [28] and taken to be 10 points. Considering a potential loss and incomplete records of 20%, a total of at least 64 patients (32 patients in the control group and 32 patients in the intervention group) should be included in the study to detect a difference between groups with a statistical power of 80% (two-sided type I error of 0.05).

### 2.9. Statistical Methods

The results will be analyzed only after the follow-up of all the included patients has been completed. The questionnaire scores will be calculated based on scoring guides from the questionnaire developers. Missing questions will be processed according to these guidelines. Patients without completed SIBDQ at any study point will be excluded from the analysis. Patients who refused to participate at any point in the study will be excluded from the analysis. We plan to use the full analysis set and the per protocol set (for patients without completed SIBDQ at any study point or who refused to participate at any point in the study).

Continuous variables will be tested for normality using the Shapiro–Wilk test and presented as mean (SD) or median (IQR), as appropriate. Categorical variables will be presented as percentages. For demographic and clinical data, descriptive statistics will be used to characterize the study population and to identify erroneous values. Additionally, missing values will be analyzed to determine the randomness of these omissions.

Hypothesis testing will be conducted for primary and secondary outcomes (Table 4). Quantitative variables will be compared using the Student’s T-test or the Mann–Whitney U test, as appropriate, and qualitative variables will be compared using the Fisher’s exact test. Univariate analysis of variance and multiple linear regression will be performed to analyze the association of secondary outcomes with the primary outcome. The Benjami and Hochberg (BH) false discovery rate (FDR) approach will be used to correct for multiple comparisons (*p* < 0.05). For the variables with FDR ≤ 10%, the term “showing a trend” will be used to avoid confusion with statistically significant variables.

All the analysis will be performed using a Python version of at least 3.7.0 or an R version of at least 4.2.0. A value of *p* < 0.05 will be considered statistically significant.

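### The exclusion rules and the named analysis sets in Section 2.9 contradict each other, and read literally no stated analysis keeps all patients as randomised

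*Protocol article*

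**What the plan says.** Three consecutive statements in Section 2.9 (Statistical Methods) matter:

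1. "Patients without completed SIBDQ at any study point will be excluded from the analysis".
2. "Patients who refused to participate at any point in the study will be excluded from the analysis".
3. "We plan to use the full analysis set and the per protocol set (for patients without completed SIBDQ at any study point", with the bracket going on to add those who refused to participate.

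The full analysis set is named but given no content. On missing data, the section says that unanswered questions within a questionnaire follow the developers' scoring guides and that "missing values will be analyzed to determine the randomness of these omissions". It attaches no consequence to the result of that check and gives no method for a patient who has no 6-month score. Neither intention-to-treat nor analysis by assigned arm is mentioned anywhere in the article.

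Section 2.8 (Sample Size) sizes the trial on completers: "Considering a potential loss and incomplete records of 20"%, giving at least 64 patients, 32 per group. Section 2.7 and Table 1 place the SIBDQ at baseline and at 6 months only.

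**The concern.** Statements 1 and 2 speak of the analysis as a whole. If they are followed, any full analysis set contains only completers. The bracket in statement 3 then attaches the per protocol set to the very patients such a set normally leaves out. A statistician who follows the text therefore gets either two identical sets of completers or a per protocol set made up of non-completers. Neither can be what is wanted.

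Three things are at stake.

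- **Comparability.** Missing a SIBDQ or refusing to continue happens after allocation. Section 2.5.1 has even the baseline questionnaires completed after group assignment. Selecting on such events can undo the balance that randomisation provides, and the demands on patients between baseline and 6 months differ by arm (monthly log-in and calls in one, visits on request in the other).
- **Data thrown away.** The rules are not confined to the primary outcome. A patient who lacks only a SIBDQ also leaves the comparison of, for example, leukopenia, which Table 3 takes from the health record and blood count. A patient with a 6-month SIBDQ but no baseline one may be dropped, although Table 4 states the hypothesis for values at 6 months.
- **Freedom after the fact.** With contradictory definitions, the analysis population can be settled once the data are known.

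**Working it through.** **Inputs.** From Section 2.8: "The standard deviation was taken to be 12.52 points"; the expected difference is "taken to be 10 points"; power 80%, two-sided alpha 0.05; 20% loss; 32 per group. From Section 2.4: 1:1 allocation.

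**Step 1: reproduce the plan's figure.** n per arm = 2 × (1.96 + 0.842)² × (12.52/10)² = 24.6, so 25. Allowing for loss, 25/0.8 = 31.25, so 32 per arm and 64 in total. With the t-distribution, 25.6 per arm are needed, and 25.6/0.8 = 32.0. The stated 64 reproduces, and this point does not change it.

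**Step 2: patients removed.** 0.20 × 64 = 12.8, about 13 patients (6.4 per arm), leaving about 51. The t-test has 80.0% power with 25.6 completers per arm. It would have 88.2% if a score were obtained from and analysed for all 32.

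**Step 3: the readings side by side.**

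| Reading | Full analysis set | Per protocol set | Agrees with statements 1 and 2? |
|---|---|---|---|
| Statements 1 and 2 govern everything | completers | the same completers | yes, but the two sets coincide and the bracket is wrong |
| Bracket taken literally | completers | the non-completers | no, because excluded patients are analysed |
| Conventional intent | all randomised | completers | no, because excluded patients are in the full set |

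Only the third reading keeps all patients as randomised, and the text rules it out.

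**Step 4: possible bias, simple algebra.** Suppose a proportion d of an arm is excluded and the excluded score g points lower than the completers. The completer mean then exceeds the arm mean by d × g, and the bias in the difference is (d₁ − d₀) × g. The documents give neither g nor a split of loss by arm. Assuming g = 5 to 10 points:

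- Loss of 20% in each arm: (0.20 − 0.20) × g = 0.
- Loss of 30% and 10% (20% overall): 0.20 × 5 = 1 point to 0.20 × 10 = 2 points, favouring whichever arm loses more.

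**Step 5: possible bias, simulation.** Assumptions: no true effect, SD 12.52, 32 per arm, 6 per arm excluded, t-test at two-sided 0.05. The strength of dependence is the log-odds of exclusion per SD of worse outcome.

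| Dependence | Mean spurious difference | Rejection rate |
|---|---|---|
| none | about 0 | about 5% |
| 0.5, one arm only | about 1 point | about 7% |
| 1, one arm only | about 2 points | about 10% |
| 2, one arm only | about 3 points | about 18% |
| 1 or 2, both arms alike | about 0 | about 6 to 8% |

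The sign follows the arm in which loss depends on outcome and reverses if the arms are swapped. The design difference is 10 points.

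**The case against.** The strongest reply is that the bracket is clumsy English: the authors meant a full analysis set of everyone randomised and a per protocol set without the listed patients, with details in an analysis plan not shown. That intent is plausible. It does not rescue the text, because it contradicts the two unqualified exclusion sentences, so some wording must change whichever reading was meant. Nor is this detail left to another document, since the article states the exclusion rule outright.

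Other parts of the reply stand and limit the point:

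- A reader might infer that telemonitoring patients who stop using the platform are excluded. The article does not say so. Section 2.5.2 requires monthly log-in but attaches no analysis consequence to it. A patient who stops logging in, has not refused participation and completes both SIBDQs stays in.
- A reader might infer that the exclusions favour telemonitoring. The documents do not support a direction. Both arms face readmission, colonoscopy with biopsy and the full questionnaires at 6 months (Section 2.5.3), so controls can refuse too. Controls also have no scheduled contact in between, so their loss could be as large or as selective.
- The simulated figures rest on an assumed dependence in one arm only. With the same dependence in both arms, the mean bias vanishes.
- The plan does budget for 20% loss and does look at the pattern of missing values. Neither step puts the excluded patients back.

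**Conclusion.** The point holds as a contradiction in stated rules. The two exclusions apply to the analysis as a whole, the full analysis set is undefined, and the per protocol set is tied to the wrong patients. Followed literally, about 13 of 64 randomised patients are lost to every analysis, if the plan's own 20% materialises.

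Confidence is high on the wording and low on the consequence. Bias could be nil; 1 to 3 points and a false-positive rate up to about 10 to 18% are what assumed one-sided, outcome-dependent loss would produce, not a forecast. It is also unclear whether the phrase about any study point means a score missing at either visit or at both; the literal conclusion takes it as either. The text should be corrected before the data are analysed.

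**What to change.** Delete the two blanket exclusion sentences and replace the sentence on analysis sets with the following.

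- **Full analysis set (primary):** all randomised patients in the arm assigned. Seek and use every 6-month SIBDQ regardless of adherence or withdrawal from the intervention, unless consent for data use is withdrawn. Analyse each secondary outcome in everyone who has it, whether or not the SIBDQ is complete.
- **Missing 6-month SIBDQ:** state a method, for example multiple imputation using baseline SIBDQ, diagnosis (UC or CD) and baseline activity. Imputation from baseline variables does not by itself remove bias when loss depends on the unseen outcome, so add a delta-shift sensitivity analysis that makes the missing scores progressively worse, separately by arm.
- **Per protocol set (supportive only):** the set that leaves out patients without both SIBDQs or who refused participation.

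The imputation model is a suggestion; the set definitions are the essential change. The cost is revised wording, some extra programming, the effort of collecting 6-month scores from patients who have left the intervention, and possibly a less favourable estimate. The sample size of 64 stays as it is.

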### 3.4. Limitations

The study has some limitations. One potential limitation is an uneven distribution of patients with UC and CD within the groups. Due to envelope randomization, there may be differences in the number of participants with UC or CD between the face-to-face and telemonitoring groups. Furthermore, the study does not intend to perform subgroup analysis based on a specific disease, such as UC or CD.

Another limitation of this study is that it is a single-center study. Different hospitals may have slightly different approaches to face-to-face management of patients. Additionally, patients in the groups may differ in the activity and severity of their IBD course, which could impact the therapy they receive during the study period.

Furthermore, the use of a website as a telemedicine intervention may also be a limitation. This approach requires patients to have certain technical equipment and computer literacy, which could reduce the number of study participants.

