Endoscopic activity of CD	Endoscopic activity of CD assessed via colonoscopy	Simple Endoscopic Score for Crohn’s Disease (SES-CD)	0–2—remission; 3–6—mild severity; 7–15—moderate severity; >15—severe;
Histological activity of IBD	Histological activity of IBD assessed via biopsy	Binary scale	No signs of inflammation in the histological material; Presence of signs of inflammation in the histological material
Laboratory tests	White blood cells concentration; Haemoglobin concentration; C-reactive protein concentration; Fecal calprotectin concentration;	Blood test and stool test	Normal values: 4–11 × 10^9^ cells/L; 120–170 g/L; 0–5 mg/L; <200 µg/g for patients with initially normal levels. <800 µg/g in both time-points for patients included in the trial with initially high levels
General medication adherence differences	Adherence to the prescribed medications, interpreted in 5 levels of adherence	GMAS score	0–10—poor adherence; 11–16—low adherence; 17–26—partial adherence; 27–29—good adherence; 30–33—high adherence;
Rate of non-scheduled medical encounters *	Unplanned visits to the Physician for IBD symptoms	As recorded in electronic health record	Number of non-scheduled visits
Rate of surgical interventions *	Surgical interventions for IBD complications	As recorded in electronic health record	Number of surgical interventions
Rate of hospitalizations *	Unplanned hospital admissions for any reason	As recorded in electronic health record	Number of unplanned hospitalizations with specification of the reason

* we assume that telemonitoring will lead to decrease in these parameters.

**Table 4 jcm-13-07734-t004:** Hypotheses proposed according to the primary and secondary study aims.

*Hypothesis*	**H_0_**	**H_a_**	
	6 months after the start of observation, there is no difference between the groups on the evaluated parameter	6 months after the start of observation, the values of the assessed parameter are higher in the telemonitoring group	6 months after the start of observation, the values of the estimated parameter are lower in the telemonitoring group
Outcomes	All primary and secondary outcomes	HRQol Generic QoL General medication adherence Satisfaction with medical care	Clinical activity of UC/CD Rate of leukopenia in patients taking immunomodulators (thiopurines, cyclosporine, tacrolimus) Depression and anxiety Visceral sensitivity Alexithymia

H_0_—null hypothesis; Ha—alternative hypothesis.

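### The primary comparison leaves the baseline SIBDQ unused and does not fix whether the result is a mean difference or a rank comparison; one prespecified adjusted model would settle both, provided baseline is taken before allocation is known

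*Protocol article*

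**What the plan says.** Section 2.9 (Statistical Methods) sets the between-group test for all quantitative outcomes: "Quantitative variables will be compared using the Student’s T-test or the Mann–Whitney U test, as appropriate". The paragraph before it names the Shapiro–Wilk test, but for deciding how continuous variables are summarised (mean and SD, or median and IQR). The only regression in the section relates secondary outcomes to the primary one; it does not adjust the treatment comparison.

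Table 4 states the null hypothesis for every primary and secondary outcome on the value at follow-up: "6 months after the start of observation, there is no difference between the groups on the evaluated parameter".

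Section 2.7 and Table 1 have SIBDQ measured at baseline and at 6 months. Section 2.9 excludes patients who lack it at either time. Section 2.5.1 places completion of the baseline questionnaires after the group has been assigned.

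Section 2.8 bases the sample size on a difference in means: "The standard deviation was taken to be 12.52 points" and the expected difference was chosen "and taken to be 10 points". Section 3.4 (Limitations) notes that the UC/CD mix may be uneven and that "patients in the groups may differ in the activity and severity of their IBD course".

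**The concern.** Two things are fixed badly.

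First, a baseline measurement of the primary outcome is collected, and under the exclusion rule every analysed patient has one, yet the treatment comparison does not use it. If baseline SIBDQ predicts 6-month SIBDQ, precision already paid for is discarded. Part of any chance baseline difference between two small arms also stays in the estimate. Section 3.4 acknowledges possible differences in disease activity, severity and diagnosis and offers no analytic remedy.

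Second, the primary test is left as a choice between two procedures that answer different questions. A t-test concerns the mean difference, the quantity for which the trial is sized. A Mann–Whitney test concerns the ordering of scores in the two arms. The test sentence gives no criterion. The nearest candidate is the Shapiro–Wilk test, so by inference the trial's own data would decide which quantity becomes the primary result.

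**Working it through.** **Inputs.** From section 2.8: SD 12.52, difference 10, "two-sided type I error of 0.05", power 80%, loss 20%, 32 per arm. From Table 3: SIBDQ range 10 to 70. Not in the documents, and therefore assumed over a range: the correlation r between baseline and 6-month SIBDQ.

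**1. The plan's own figure.** Per arm, by the normal approximation: 2 × (1.960 + 0.842)² × 12.52² / 10² = 24.6, so 25. Allowing for loss: 25 / 0.8 = 31.25, so 32 per arm and 64 in total. The stated figure reproduces.

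Conversely, 32 × 0.8 = 25.6 completers per arm. The unadjusted standard error is 12.52 × √(2/25.6) = 3.50, and power from the noncentral t distribution is 80.0%. The sample size is right for an unadjusted t-test.

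**2. Adding baseline SIBDQ and diagnosis.** Diagnosis is assumed to explain nothing further, which is the cautious case. With 2 × 25.6 = 51.2 patients and two covariates:

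- residual SD = 12.52 × √(1 − r²);
- variance inflation for estimating two covariate effects = 1 + 2/(51.2 − 5) = 1.043;
- SE = residual SD × √(2/25.6 × 1.043);
- degrees of freedom = 51.2 − 4 = 47.2, two-sided critical t = 2.012;
- power from the noncentral t distribution with noncentrality 10/SE.

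| Analysis | Residual SD | SE | 10/SE | Power |
|---|---|---|---|---|
| Unadjusted | 12.52 | 3.50 | 2.86 | 80% |
| r = 0 | 12.52 | 3.57 | 2.80 | 78% |
| r = 0.2 | 12.27 | 3.50 | 2.86 | 80% |
| r = 0.3 | 11.94 | 3.41 | 2.93 | 82% |
| r = 0.4 | 11.47 | 3.28 | 3.05 | 85% |
| r = 0.5 | 10.84 | 3.10 | 3.23 | 89% |
| r = 0.7 | 8.94 | 2.55 | 3.92 | 97% |

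Break-even is near r = 0.2.

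**3. Chance imbalance.** If the same SD holds at baseline, the difference in baseline means between arms has a standard error of 3.50 points, against a target effect of 10. With equal SDs at the two times, r times the imbalance carries into the unadjusted estimate. At r = 0.5, an imbalance of 3.5 points shifts it by 0.5 × 3.5 = 1.75 points.

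**4. Choosing the test by a normality check.** This was simulated with 25 per arm and 4,000 runs per setting. Scores were rounded and limited to 10–70, with an assumed control mean of 48. Mann–Whitney was used if Shapiro–Wilk gave p < 0.05 in either arm.

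- No effect: type I error was 5.3–5.9% for the two-step procedure and 5.4–5.6% for the plain t-test. Monte Carlo error is about √(0.05 × 0.95 / 4000) = 0.35 points. Mann–Whitney was chosen in 9–10% of runs.
- A 10-point effect: power of the two-step procedure was 78–79%, as for the plain t-test. Mann–Whitney was chosen in about 56% of runs, because a telemonitoring mean of 58 lies only (70 − 58)/12.52 = 0.96 SD below the ceiling.

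So under these assumptions error rates hardly move, but which quantity is reported as primary is close to a coin toss when the planned effect is present.

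**The case against.** The strongest reply is that nothing here is an error. An unadjusted comparison is valid under randomisation, its standard error already allows for chance imbalance, and the sample size matches it. All of that stands: this is a loss of efficiency and of prespecification. It does not follow that the matter can be left to an unseen analysis plan, because section 2.9 and Table 4 themselves fix an unadjusted comparison of 6-month values by one of two tests.

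Several stronger readings are tempting and are not supported:

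- *The protocol says Shapiro–Wilk selects the test.* It ties that check to data presentation; the link to the choice of test is an inference, though the natural one.
- *The two-step choice inflates type I error.* The simulation shows no clear inflation.
- *Adjustment gains power for free.* The gain depends on a correlation that the documents do not give. A low value cannot be excluded, since baseline is taken around a hospital treatment episode and the outcome six months later.
- *Baseline imbalance passes in full into the estimate.* Only the share r does.
- *The protocol expects the arms to differ.* Section 3.4 says only that they may.

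One further objection changes the remedy. With the baseline questionnaires completed after assignment and no blinding described, patients may answer knowing their arm. Adjusting for a covariate affected by that knowledge can itself bias the treatment effect, so the model is a clean remedy only with a pre-allocation baseline.

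**Conclusion.** The point holds as a recommended change. The planned analysis is valid and correctly sized, but it leaves a measured baseline unused and does not settle whether the primary result is a mean difference or a rank comparison.

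The size rests on the unstated correlation. Relative to 80% power, adjustment costs about 2 percentage points at r = 0, breaks even near 0.2, and gains about 2 at 0.3, 5 at 0.4, 9 at 0.5 and 17 at 0.7. These figures assume SD 12.52, a 10-point effect, 25.6 completers per arm and no contribution from diagnosis. The case for fixing one estimand does not depend on r.

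A reader might infer that the primary analysis is invalid or that 64 patients is wrong. Neither follows.

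**What to change.** Prespecify one primary analysis in section 2.9: a linear model of 6-month SIBDQ on arm, baseline SIBDQ and diagnosis (UC or CD), reporting the adjusted mean difference with its 95% CI. Keep a rank test as a sensitivity analysis only, and state that no normality check selects the primary test. Align Table 4 with this.

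Use the same approach for the other continuous scales measured at baseline. For DAI and CDAI leave out diagnosis, since each is scored in one disease only and diagnosis would be constant in the model.

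In section 2.5.1, have the baseline SIBDQ, and any other scale used as a covariate, completed before the envelope is opened. Where patients have already been randomised under the present order this cannot be undone, so show the unadjusted difference alongside.

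Cost: analysis wording, one or two degrees of freedom, and a small change in the order of baseline procedures. No additional patients or measurements are needed. The change should be made before outcome data are examined; section 2.9 defers analysis until all follow-up is complete.

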### 2.4. Randomization

Randomization will be performed in 1:1 ratio between control and experimental groups using the envelope method.

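### Section 2.9 names Student's t-test with only a normality check; if analysed arms differ in both size and spread, mainly in the UC-only and CD-only comparisons, its error rate drifts from 5%, and Welch's test avoids this at almost no cost

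*Protocol article*

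**What the plan says.** Section 2.9 sets the between-arm test for all quantitative outcomes: "Quantitative variables will be compared using the Student’s T-test or the Mann–Whitney U test", with the choice between the two left to whichever is appropriate. The stated assumption check concerns shape: "Continuous variables will be tested for normality using the Shapiro–Wilk test and presented as mean (SD) or median (IQR), as appropriate". That this check also decides between the two tests is implied but not written. Equality of variances is not mentioned, and Welch's version is not among the named options.

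On arm sizes, section 2.4 says: "Randomization will be performed in 1:1 ratio between control and experimental groups using the envelope method". Section 2.8 plans 32 patients per arm, including an allowance of 20% for loss and incomplete records. Section 2.9 then removes patients who lack a completed SIBDQ at any point or who refuse to continue. Table 3 lists DAI (UC only) and CDAI (CD only) as separate secondary outcomes. For these the Limitations (3.4) concede: "there may be differences in the number of participants with UC or CD between the face-to-face and telemonitoring groups".

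On spread, the sample size section uses one value for both arms: "The standard deviation was taken to be 12.52 points". No arm-specific SDs are given anywhere.

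**The concern.** Student's test estimates one common variance. When arm sizes match, the pooled standard error is right on average even if the variances differ. When both sizes and variances differ, it is not. If the smaller arm is the more variable one, the standard error is too small and false positives exceed 5%. If the larger arm is the more variable one, the test is conservative and power is lost. A Shapiro–Wilk test does not detect either situation.

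Unequal analysed numbers are realistic in two places. One is the disease-specific comparisons just described. The other is the whole sample after exclusions, because one arm is telephoned monthly and the other is seen on request, so completion could differ. Unequal spread is possible but not established: on scales with a floor or ceiling, an arm that moves towards the bound can become less variable.

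**Working it through.** **1. The plan's own figure.** Inputs from section 2.8: SD 12.52, difference 10, 80% power, two-sided 0.05, 20% loss.

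n per arm = 2 × (1.960 + 0.842)² × (12.52/10)² = 24.6, rounded up to 25. Then 25/0.8 = 31.25, rounded up to 32 per arm and 64 in total. The stated 64 is reproduced. It assumes one SD and equal arms.

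**2. How far the pooled standard error can be off.** Ratio of pooled to true standard error:

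√{[((n₁−1)s₁² + (n₂−1)s₂²)/(n₁+n₂−2)] × (1/n₁ + 1/n₂) ÷ (s₁²/n₁ + s₂²/n₂)}

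- 10 v 16, smaller arm with 1.5 times the SD: pooled variance (9 × 2.25 + 15 × 1)/24 = 1.469; × 0.1625 = 0.2387; true 0.225 + 0.0625 = 0.2875; ratio √0.830 = 0.91, so 9% too small.
- 16 v 10, larger arm with 1.5 times the SD: pooled variance (15 × 2.25 + 9 × 1)/24 = 1.781; × 0.1625 = 0.2895; true 0.1406 + 0.1 = 0.2406; ratio √1.203 = 1.10, so 10% too large.
- Equal arms: ratio exactly 1 whatever the variances.

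**3. Type I error.** Simulation with normal data, equal means, nominal 5%, one million runs per row. The first number in each split is the arm with the larger SD.

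| Split | SD ratio | Student | Welch |
|---|---|---|---|
| 32 v 32 | 1.5 | 5.1% | 5.0% |
| 26 v 26 | 1.5 | 5.1% | 5.0% |
| 24 v 28 | 1.14 | 5.2% | 5.0% |
| 24 v 28 | 1.5 | 5.8% | 5.0% |
| 28 v 24 | 1.5 | 4.4% | 5.0% |
| 10 v 16 | 1.14 | 5.7% | 5.0% |
| 10 v 16 | 1.5 | 7.4% | 5.1% |
| 16 v 10 | 1.14 | 4.4% | 5.0% |
| 16 v 10 | 1.5 | 3.4% | 4.9% |

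Other simulation runs at 10 v 16 gave 5.6% to 5.8% at ratio 1.14 and 7.3% to 7.6% at ratio 1.5.

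**4. Where the assumed values come from.**

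- *SD ratio 1.14.* This is what the SIBDQ bounds (10 to 70, Table 3) would give for the full planned effect under an assumed scaled beta distribution with constant precision, control mean 45 and SD 12.52. Rescaled to 0–1, the means 45 and 55 become 0.583 and 0.75. The ratio is √[(0.583 × 0.417)/(0.75 × 0.25)] = √1.296 = 1.14, so the SD falls from 12.52 to 11.0.
- *SD ratio 1.5.* An assumed upper value; the article gives nothing to fix it.
- *10 v 16.* If 26 of 64 patients have CD (an assumption) and arms are 32:32, the hypergeometric probability of a 10:16 split or worse, in either direction, is 0.20.

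**5. Cost of Welch when variances are equal.** Power at an effect of 0.8 SD (10/12.52), Student then Welch: 25 v 25, 79.1% and 79.1% (loss 0.1 point before rounding); 21 v 30, 78.7% and 78.5% (0.3 point before rounding); 9 v 17, 46.2% and 44.7% (about 1.6 points).

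**The case against.** The case for leaving the text alone is substantial.

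- **Balanced arms are protected.** At 32 v 32 or 26 v 26 Student's test is essentially unaffected. This stands, and it covers the primary comparison as planned.
- **Bounds do not by themselves make variances unequal.** A reader might infer that bounded scales guarantee different spreads and so inflate false positives. The article does not support that. If the two score distributions are identical, their variances are equal and Student's test is valid. The bounds change the spread only when the means shift, and under the beta model the planned SIBDQ effect gives a ratio of only 1.14. Ratios of 1.3 to 1.5 under equal means have to be assumed.
- **Large imbalance in the whole sample is unlikely.** With independent 20% loss in both arms of 32, a gap of 9 or more completers (such as 21 v 30) has a probability of about 0.8%. Strongly differential loss could produce it, but the article does not predict that.
- **Inflation needs the right direction.** The 20% for a 10:16 split counts both directions; the split with the more variable arm smaller has about half that probability, and only if the variances differ.
- **Some scales may not reach a t-test.** The section allows Mann–Whitney where appropriate, and skewed scores near a floor (DAI, HADS) may go there, where this change does nothing.
- **Intervals.** A reader might add that confidence intervals would be too short. Section 2.9 plans none, so no stated interval is wrong.
- **Level of detail.** The choice of t-test version can be left to an analysis plan. Here, however, the article does name a test, and the usual meaning of that name is the pooled one, although it never uses the words equal variance. The phrase allowing discretion offers a choice between two named tests, and Welch is neither.

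These points reduce the size of the concern. They do not give a reason to prefer the pooled version.

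**Conclusion.** The point holds as a minor, nearly free improvement. The named t-test relies on equal variances or equal analysed arms. The article does not check the first, and its own Limitations say the second may fail for the disease-specific outcomes. At 10 v 16 and SD ratios of 1.14 to 1.5, the nominal 5% becomes about 5.7% to 7.4%, or about 4.4% to 3.4%, depending on which arm is more variable. At a mild imbalance of 24 v 28 and ratio 1.14 it is 5.2%. The disease split, the SD ratios and normality are assumptions; the documents give none of them. Neither the primary comparison at the planned 32:32 nor the sample size of 64 is called into question.

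**What to change.** In section 2.9, replace *Student's T-test* by *Welch's t-test (unequal variances)* wherever a t-test compares the two arms. Settle this before any outcome data are analysed, so that the choice between pooled and unpooled versions is not made later. No variance pre-test is needed.

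The cost is one phrase. Both R and Python, the software named in the section, provide the test. The sample size does not change, and the power cost is the small one shown above, noticeable only in very small and lopsided subsets.
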